### Ethical approval

This study has been approved by the Ethic Committee of the (blinded for review; Ethics Committee No.: 2021/136) and has been registered in the German Clinical Trials Register (DRKS-ID: DRKS00027156; AV: 17 November 2021, original, AV: 23 February 2022, amendment 01). The primary reason for the amendment was a refinement of hypotheses. Additional modifications will be reported to the German Clinical Trials Register. Written informed consent from each participant will be obtained and stored on the Aeroscan servers, which are hosted by the Domain Factory in Germany (see Data management plan for more details).

### Study procedure

The current protocol focuses exclusively on the evaluation plan of a one-arm, multicenter mHealth interventional study and the post-hoc description of the Habit Coach app (i.e., after the development phase of the app). The trial is undertaken by independent external research experts in health and exercise psychology, presenting an important quality criterion for the project. Figure 2 depicts the study flow. Through the registration process in the app, written informed consent will be obtained from individuals. Upon registration, participants receive a 100-days access to the Habit Coach app. Besides the usual features, the app includes four interactive worksheets to aid the habit formation process, which have been specifically developed for this study by the team of independent experts in health and exercise psychology.

**Fig. 2 Fig2:**
[figure not shown]
Study flow. Note. Interactive worksheets have been added to the Habit Coach by the team of independent experts in health and exercise psychology

### Description of the app

The app has been developed by the Aeroscan GmbH (limited liability company) and consists of different versions that each fit a specific work context (e.g., home office program, nursing program). The present study exclusively focuses on the nursing program, which is available as a progressive web-app since March 2020. An updated single-page-app is available since November 2021, which will be included in the present study. The app is compatible with desktops and all kinds of mobile devices. The app is accessible only through specific booking codes provided by the Aeroscan company (i.e., not available in common app-stores). A multidisciplinary team consisting of professionals with expertise in nursing, sports and exercise science, physiotherapy, nutrition, stress management and human–computer interactions were involved in the planning and development of the app content and features. The app was devised in iterative processes, involving input from both target group members (i.e., health care professionals) and experts. All within-app exercise and task suggestions were designed to be implemented in daily routines (i.e., within and outside the work context), and in close collaboration with the nurses (i.e., participatory approach) to enhance both personal relevance and acceptance of the app content. Programming of the app was conducted by the Aeroscan IT, being responsible for all tasks related to computer science (i.e., programming of app, surveillance of data servers, etc.).

### Description of the intervention

In order to promote better reporting of interventions, we used the template for intervention description and replication (TIDieR) checklist ([59], [Additional file 2]). The intervention consists of a mobile app (the Habit Coach) with a 100-days access and interactive worksheets, targeting healthy habit formation for the behaviors physical activity, nutrition and mindfulness in health care professionals (Fig. 2). Participants are supported during the entire behavior change process (Fig. 1) to set individual health goals, develop action plans and self-monitor one’s goals in order to facilitate healthy habit formation for multiple health behaviors. The interactive worksheets have been conceptualized by the team of independent experts in health and exercise psychology and added to the regular app-features. The app is location-independent and can be used in and outside the hospital context.

Upon the account creation, participants receive a booking confirmation mail together with the first interactive worksheet called “Selecting favorites” (booking date + 0, [see Additional file 3A]). Through this worksheet, participants are encouraged to select their favorite physical activity, nutrition, and mindfulness exercises and tasks from the within-app catalog within the first couple of weeks and to mark these as favorites (by means of a bookmark symbol, [see Additional file 4A]). Additionally, participants are informed about the importance of repeating selected exercises and tasks in stable contexts as opposed to continuously selecting new exercises. Allowing participants to choose their favorite exercises and tasks enhances their need for autonomy satisfaction and their positive outcome expectancies. Furthermore, by offering participants to choose to incorporate their favorite exercises and tasks in their daily routines (as opposed to only within or outside the work context), reduces negative outcome expectancies (e.g., lack of time). Participants are encouraged to repeat these favorite exercises and tasks on a daily basis over the 100-days period in order to foster cue-behavior associations and therefore habit formation. To ensure that none of the participants misses out on selecting favorite exercises and tasks, a reminder email is sent.

After the account creation, participants will be asked to characterize their job profile, to define their interests in health related topics, to set a personal health goal and to estimate their current physical activity, nutrition and mindfulness behaviors as well as their knowledge with regard to these three behaviors. This so-called wizard (Additional File 4B) is used to tailor the app’s content to participants’ needs, work and private (i.e., family) situation, and personal preferences/interests in health and wellness-related topics (e.g., sleep quality, brain gym, healthy snacks, outdoor activities, cooking with kids). This tailoring will increase the personal relevance of the app content and enhance adherence to the intervention overall. Although the wizard is displayed with the first log-in, participants can make changes to their preferences and interest by filling in the wizard a second or third time during the intervention period. Changes in the wizard (i.e., preferences) will result in changes in offered content but not in changes in self-chosen favorites to prevent disruptions to the habit formation process. In order to facilitate the setting of a personal health goal, participants have the opportunity to download an interactive worksheet (called “Goal setting”, [see Additional file 3B]). This goal setting worksheet provides participants with step by step instructions on how to form “SMART” health goals (i.e., goals that are specific, measurable, achievable, relevant, time bound).

Next, participants are guided through an onboarding process, intended to explain the app’s features and functions. The Habit Coach app is constructed to follow the theme “well-being through balance” for each of the target behavioral domains: physical activity, nutrition and mindfulness. To track and self-monitor balance in all three domains, a progress bar is displayed on the home screen, indicating the average positive and negative progress in each behavioral domain of the last seven days [see Additional file 4A].

The within-app catalogue of physical activity, nutrition, and mindfulness exercises consists of a variety of exercises and tasks differing in duration, intensity and target (e.g., stretching, walking; [see Additional file 4C]). These exercises and tasks are embedded in specific situations/contexts (e.g., during lunch breaks, while preparing medication, during team meetings, on the way home, while playing with kids) encountered by health care professionals throughout the (work)day. It is expected that these everyday situations/contexts will elicit the desired behavior automatically over time after almost daily repetition of that behavior in stable situations/contexts. All physical exercises are explained with a short video, featuring a nurse (dressed as such) engaging in a given exercise. The nurse should function as a role model for participants. Furthermore, exercise and task suggestions consist of a) activity elements intended to motivate participants to take action and b) knowledge elements supposed to motivate participants to learn something new [see Additional file 4D]. Lastly, exercise and task suggestions rotate regularly and rotation depends on participants’ balance progress. As soon as participants engage in an exercise or task, they can tick a box to indicate that they have completed the exercise or task, which provides them with points. Collecting points, as a gamification element, translates into the progress bars and is intended to increase engagement with the intervention. For instance, in case a participant is mainly interested in nutrition and mindfulness tasks during a week, positive progress is made in the areas of nutrition and mindfulness, and negative progress is made for physical activity. To restore balance among all three behaviors, participants will automatically receive more suggestions for physical activity the upcoming week and fewer for nutrition and mindfulness topics. In addition, new suggestions can additionally be generated by clicking the “new suggestions” button.

Additionally, the home screen features so-called “highlights of the day”, including blog articles with health-related topics, as well as promotion of events within hospital/institution [see Additional file 4E]. Moreover, the “open tasks” feature on the home screen summarizes all exercises and tasks that have been started once but never completed, pending assessments as well as all exercises and tasks marked as favorites [see Additional file 4E]. The “open tasks” feature functions as a reminder to continuously repeat the self-selected favorite exercises and tasks, to keep participants accountable and as such to promote the habit formation process. Lastly, participants have the opportunity to contact a trained coach specialized in physical activity, nutrition and mindfulness practices (via phone or email) from the Aeroscan company, in case of questions, technical issues, to inquire information on health-related topics or request support in forming habits [see Additional file 4F].

To further facilitate the habit formation process, two additional interactive worksheets (i.e., worksheet “cue selection” and worksheet “action planning”, [see Additional file 3C and D, respectively]) are sent to participants via newsletters (booking date + 14 and + 25, respectively). The worksheets feature information and prompt to a) determine everyday cues for action, which thus far did not result in automatic health behavior but in which participants wish to be more active, eat healthier or relax more in the future (e.g., during the lunch break, during medical rounds) and b) to develop if–then action plans for each of the three behaviors in order to specify when, where, and how an intended behavior will be executed (e.g., “If it is time for a lunch break, then I will eat an homemade salad”). The following criteria for choosing everyday situations (i.e., cues) have been formulated: something that a) occurs multiple times per week and b) with a given regularity.

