**Stage 1 – motivational**		
Goal setting (1.1) Goal setting outcome (1.3)	Behavioral regulation (intention) Goals	During the initial wizard, intended to tailor the app’s content at best possible to participants’ needs, work and private situation, participants are asked to set an individual health goal. An interactive goal setting worksheet is available to support participants in setting goals correctly. Note, participants are not specifically guided to differentiate between behavioral (e.g., set the goal of eating 5 pieces of fruit per day) and outcome goals (i.e., set a weight loss goals of 0.5 kg per week) but to choose a personally relevant health goal
Instruction on how to perform the behavior (4.1) Demonstration of the behavior (6.1)	Knowledge (self-efficacy) Beliefs about capability skills Social learning/imitating	The within-app exercise and task catalogue offers videos, written information and instructions on how to perform physical activity, and mindfulness behaviors. The videos feature a nurse executing the behavior correctly. By observing and imitating the nurse, self-efficacy is enhanced and beliefs are built that participants are able to achieve what the role model (i.e. nurse) achieved, raising expectations of success and motivating participants to work hard towards their goals
Information about health (5.1) and emotional (5.6) consequences	Knowledge Beliefs about consequences (positive, negative outcome expectancies) Attitude towards the behavior Perceived susceptibility/ vulnerability Intention Emotion	Blog articles (“highlights of the day”), covering different health topics related to physical activity, nutrition and mindfulness behaviors, are presented on the home screen and offering information about positive and negative health consequences, affecting participants’ knowledge, outcome expectancies, attitudes, perceived personal risk, emotional state and in turn their intentions. Additionally, “knowledge elements” of exercise and task suggestions included in within-app exercise catalogue offer information about health consequences that are supposed to have similar effects on aforementioned social-cognitive variables

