### Evaluation design

A one-arm, multicenter mHealth interventional study will be performed. Participants complete all assessments in the app with the same assessment rhythm irrespective of when participants enroll in the study. Upon registration, participants can complete questions on socio-demographic variables, psycho-social determinants (e.g., intention, self-efficacy), physical activity, nutrition and mindfulness as well as health-related outcomes (e.g., back pain). Data will be collected across a 100-day period at four assessment points: baseline (booking date + 0), interim after 4 weeks (booking date + 28) and 8 weeks (booking date + 56) and post-intervention (booking date + 99). Additionally, 11 weekly assessments will be scheduled (booking date + 7, + 14, + 21, + 35, + 42, + 49, + 63, + 70, + 77, + 84, + 91). Participants will receive reminder emails for the baseline and post assessment four days after the respective assessment date (i.e., baseline reminder booking date + 4 days, post assessment booking date + 104 days). Reminders for the remaining assessments are incorporated into the app (via “open tasks”, see Description of the intervention for further information). Outcome data will be the same for all participants, whether they continue or discontinue/deviate from the intervention protocol. One week after the completion of the intervention, a structured interview is scheduled with volunteers to gain insights in participants’ experiences with the app (e.g., practicability, operability, acceptability). Due to economic reasons, the total set of items varies per assessment point. The Fig. 3 presents an overview of the enrolment schedule, the intervention, worksheets and assessments.

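### Nothing in the text puts the baseline form before the goal-setting wizard and first worksheet, so baseline intention and outcome expectancies may follow first exposure for some participants

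*Protocol article*

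**What the plan says.** In the Protocol article, Description of the intervention sets out the first contact with the app. On opening an account the participant is sent intervention material at once: "Upon the account creation, participants receive a booking confirmation mail together with the first interactive worksheet". This is the Selecting favorites worksheet, dated booking date + 0. The wizard asks participants, among other things, "to define their interests in health related topics, to set a personal health goal", and its timing is given in the clause "Although the wizard is displayed with the first log-in". An onboarding tour follows. The home screen has an open-tasks list that includes "pending assessments as well as all exercises and tasks marked as favorites".

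Evaluation design places all assessments in the app and dates the baseline at booking date + 0 as well: "Upon registration, participants can complete questions on socio-demographic variables, psycho-social determinants (e.g., intention, self-efficacy", with further items on behavior and health. A baseline reminder e-mail goes out at booking date + 4. Data management names informed consent as the condition for access to the app and names no other.

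The protocol also states what the early content is meant to do. The goal-setting row of Table 1 ("During the initial wizard, intended to tailor the app’s content at best possible to participants’ needs") gives intention as the mechanism. Description of the intervention says that choosing favorites raises positive outcome expectancies, and that fitting them into daily routines lowers negative ones. Objectives lists intention and outcome expectancies, with self-efficacy, as the hypothesis 1b outcomes.

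**The concern.** A baseline-to-post comparison needs a baseline taken before the intervention begins to act. Here two intervention components and the baseline form fall on the same day, and the text does not say that the form must be submitted first. The plan does rely on an unexposed start: Process evaluation leaves out the app-related items at t0 because participants do not yet know the app.

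Two sets of results are at stake. In hypothesis 1b, any early lift in intention or outcome expectancies is counted as baseline and so removed from the measured change. In hypotheses 2-4 the same baseline values are predictors. If some were recorded after exposure, they combine what participants brought to the study with how they first reacted to the app, in proportions that depend on how each person moved through the first screens.

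**Working it through.** **Order of events as the text gives it**

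- Account creation, day 0: booking confirmation with the Selecting favorites worksheet (Description of the intervention).
- First log-in: wizard with a personal health goal, then onboarding (same section).
- Day 0: baseline form available upon registration (Evaluation design).
- Day + 4: e-mail reminder for the baseline form (Evaluation design). The plan therefore expects some forms to be outstanding four days after the first worksheet was sent. No closing date is stated.
- Condition for app access: consent (Data management).

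The worksheet and the form thus run alongside each other. The wizard may come before the form, but no sentence says that it does, and none says that it does not.

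**Which constructs the protocol links to early content**

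- Intention: linked to goal setting in the wizard (Table 1, stage 1).
- Outcome expectancies: linked to choosing favorites. The worksheet invites this "within the first couple of weeks", so receiving it on day 0 is not the same as acting on it that day.
- Self-efficacy: linked to the catalogue's videos and instructions (Table 1). It is affected only if the catalogue is used before the form.
- Action planning: belongs to hypothesis 1c, and its worksheet is sent at day + 25.

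**Direction for hypothesis 1b**

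Let D be the true change from before exposure to post-assessment, b the mean lift already present among those who answered after exposure, and p their share. Then:

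measured change = D − p × b

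If b is in the intended direction, the measured change is too small. The same holds for negative outcome expectancies with the signs reversed.

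**Illustration on the 1-6 intention scale**

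D, b and p are all assumptions; the documents give none of them.

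- D = 0.5, p = 1, b = 0.1: 0.5 − 0.1 = 0.4, a loss of 0.1/0.5 = 20%.
- D = 0.5, p = 1, b = 0.3: 0.5 − 0.3 = 0.2, a loss of 0.3/0.5 = 60%.
- D = 0.5, p = 0.5, b = 0.1 to 0.3: the shift is 0.05 to 0.15, a loss of 10% to 30%.

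**Illustration for power**

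Statistical power gives 228 participants including 30% attrition, and 228 × 0.70 = 159.6, so take 159 analysed. Assume a paired t-test at two-sided alpha 0.05, with effects in standard deviations of the change score and the shift meaning p × b.

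| True change | Shift 0 | Shift 0.05 | Shift 0.10 | Shift 0.20 |
|---|---|---|---|---|
| 0.30 | 0.96 | 0.88 | 0.71 | 0.24 |
| 0.20 | 0.71 | 0.47 | 0.24 | 0.05 |

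The stated sample size was set for automaticity over time, not for hypothesis 1b. The table shows sensitivity and does not test that figure.

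**Hypotheses 2-4**

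For exposed participants the recorded predictor is prior motivation plus early response. If the early response is unrelated to the outcome, it acts as noise in the predictor. If it reflects engagement with the app, it may carry its own association with later habit strength. The direction of any distortion therefore cannot be stated.

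**The case against.** The strongest objection is that the order of screens is simply not given. A form available upon registration and a wizard shown at first log-in are compatible with baseline coming first. The figures with the study flow and the schedule, which could settle this, are not shown. The open-tasks list shows that unfinished forms stay visible, not that the baseline form is first offered there. All of this stands. A reader might infer from the sequence wizard, onboarding, home screen that every baseline follows goal setting; the text does not support that. Anyone who completes the form before the wizard and worksheet has a valid baseline.

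The mechanism can also be pressed too far. The wizard asks for one freely chosen health goal, whereas the baseline intention items name fixed targets in three domains. The SMART goal worksheet is an optional download. Favorites may be chosen weeks later. This makes a large same-day lift less certain, but it does not remove the link that the protocol itself draws.

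Finally, hypothesis 1 is labelled preliminary, the protocol concedes that effectiveness cannot be evaluated without a control group, and a bias towards no change is conservative. That limits the consequence for hypothesis 1b. It does not answer the point for hypotheses 2-4, which are prediction questions and include the one about habit strength at post-assessment. Motivation measured at program start is a legitimate predictor, but only if it is measured at the same point for everyone.

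**Conclusion.** The point holds as a risk that the described procedure leaves open. Baseline intention and outcome expectancies may be measured after first exposure for some participants, because nothing stated makes the form come first and late completion is foreseen. Hypothesis 1b is then at risk of bias, probably towards understating change, provided the early effect is in the intended direction. The baseline predictors in hypotheses 2-4 may mix prior motivation with early response.

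Three stronger conclusions are not supported. The documents do not show that baseline values are post-exposure in general or that hypothesis 1b is in fact biased. They do not tie action planning to day-0 content, nor self-efficacy to the wizard. They also give no size: the 20% to 60% range and the power figures are arithmetic on assumed inputs.

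**What to change.** State and program that the baseline form appears directly after consent and must be submitted before the wizard, the catalogue and the Selecting favorites worksheet are released. The worksheet would then be separated from the booking confirmation and sent on submission of the form.

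For participants already enrolled, use form and wizard timestamps, where available, to flag baselines completed after exposure. Repeat hypotheses 1b and 2-4 without the flagged participants as a sensitivity analysis. A difference between the two analyses could also reflect who chose to complete the form first, so it should be read with that in mind.

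The cost is a change in screen order and one automated e-mail. Some registrants may abandon at a mandatory form, including a few whom the day + 4 reminder might have recovered. The loss to the analysis is limited, because the Statistical analysis section already restricts it to participants with a completed baseline.
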